#### TMS measurement

A single-pulse magnetic stimulator (Magstim 200^2^) will be used to carry out all TMS studies. A Double Cone 110-millimetre (mm) coil that provides sufficient depth of penetration to reliably stimulate cortical representation of ankle musculature will be used in this study. Subjects from each intervention group will undergo TMS testing both pre- and post-intervention. The primary motor cortex of the hemisphere contralateral to the impaired ankle will be tested. The pre-intervention session will consist of (i) identifying optimal coil position ('hot spot') and motor threshold (MT) for the target leg muscles (tibialis anterior and gastrocnemius), (ii) conducting input-output (IO) curve studies of both muscles, (iii) input-output curve studies will be conducted both with the muscles at rest and with the muscles pre-activated (active contraction condition). The pre-activated condition is required to generate cortical silent period data.

Surface EMG electrodes will be attached over tibialis anterior and gastrocnemius. The EMG signal will be filtered with a bandpass of 1–1000 Hz, amplified, and digitized at 2000 Hz. The data will be graphically displayed and stored for later analysis in 600-millisecond (ms) samples beginning 100 ms before TMS onset (custom written MATLAB module for analog-to-digital sampling (dwaq; dataWizard acquisition, [name]). For the active contraction condition the subject will be asked to perform maximal dorsiflexion and maximal plantarflexion against a load cell, with care taken to minimize contribution from other muscle groups at the thigh or pelvis. The largest of three attempts is taken as the maximum voluntary contraction force (MVC).

To determine optimal TMS coil location and orientation, TMS pulses are delivered while the subject contracts the ankle musculature and at an inter-stimulus interval of 5–10 seconds. The coil is initially placed at the vertex and the optimal scalp position for TMS ('hot spot') is determined by moving the coil a few centimetres (cm) in each direction from this position and observing the site at which the largest motor evoked potential (MEP) is produced at supra-threshold intensities. The initial muscle contraction serves to facilitate induction of MEPs and is used to aid in finding the motor hot spot.

Brainsight™ Frameless is a stereotactic image guidance system that will facilitate the positioning of the TMS coil over a subject's brain (Figure 2). With Brainsight, variability in TMS measures taken at different time points will be greatly minimized as the motor 'hot spot' for each muscle is marked on a 3D reconstruction of a standard magnetic resonance image of the brain at the pre-intervention measurement and then the same hot spot location becomes the site of stimulation at the post intervention assessment. A single T1-weighted MRI Scan will be used with the interactive frameless stereotactic system (Brainsight, Rogue Industries, Canada) to guide precise location of the TMS coil and stimulate the appropriate muscle representation in M1. With Brainsight technology a 3D reconstruction of an MRI scan can be made. Subjects will sit in a chair with their head secured. Landmarks on the subject's head will be co-registered with landmarks on the structural MRI to allow tracking of the position of the TMS coil with respect to the underlying cortex. The position of the TMS coil and the subject's head are co-registered from small pieces of refractory material (trackers) placed on them. An infrared optical position sensor monitors the trackers. This information is sent to a computer, which after a calibration procedure displays the position and orientation of the coil relative to the MRI. After the motor 'hot spot' for the tibialis anterior and gastrocnemius muscles are identified, the coil location and orientation is then marked on the anatomic MRI using Brainsight. All subsequent TMS pulses will then be delivered with the coil placed in the same location and orientation as this hot spot.

**Figure 2 F2:**
[figure not shown]
**Screenshot image from Brainsight stereotactic image guidance software used to localize motor hotspot**. A 3-dimensional reconstruction (A, bottom image) of a single T1 magnetic resonance scan of the brain (B) with positioning of the transcranial magnetic stimulation coil. An infrared optical sensor co-registers the position and orientation of the TMS coil relative to small refractory markers on the subject's cranium (A, top image). This provides the investigator with real-time information regarding the brain locus that will receive TMS given a position and orientation of the TMS coil, in order to minimize spatial variability in TMS application. (Image courtesy of [name], Brainsight, Rogue Industries, Canada.).

#### Motor threshold (MT)

MT is defined as the lowest TMS intensity required to elicit a small, clearly discernable MEP at least 50% of the time (50 microvolts [μV] for resting muscles, 100 μV for muscles under active contraction). Within a given individual, MT is stable across TMS sessions which assures that suprathreshold TMS intensities expressed as a percentage of MT can be reliably compared between TMS sessions.[28]

The following procedure for determining active MT will apply for testing the tibialis anterior and gastrocnemius. Active contraction corticomotor excitability data will be collected with the muscles at 10% of the subject's MVC. The coil is oriented and positioned with the handle of the coil pointing backward to induce posterior to anterior current flow across the primary motor cortex. For determination of active MT, the subject makes a steady, minimal background contraction against a load cell (10% of MVC) with the help of audiovisual feedback. TMS pulses are delivered while the subject contracts and at an inter-stimulus interval of 5–10 seconds. The coil is initially placed at the vertex. Optimal coil location for TMS ('hot spot') is determined by moving the coil a few cm in each direction from this position and observing the site at which the largest MEP is produced at supra-threshold intensities. This optimal coil location is then marked on the 3D MRI using Brainsight and the coil is fixed at this location on the scalp using a clamp and external support. TMS intensity is then decreased by 1–2% intervals. TMS MT for the muscle is the TMS intensity where at least 5 of 10 responses generate peak-to-peak MEP amplitudes of at least 50 μV for the resting condition and 100 μV for the active contraction condition. Alterations in corticomotor system excitability will be assessed as changes in MEP and cortical silent period duration (CSP) input-output curve characteristics between pre- and post-intervention time points for the three groups. TMS intensities for this study will be expressed as a percentage of MT.

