### Research Design

Subjects each begin with pre-intervention TMS measures (motor thresholds and input-output curves), ankle range of motion (ROM) tests, and lower extremity functional behavior tests. Each pre-intervention measurement will be taken a total of 2 times with a 30 minute rest break between measurements. Subjects will then be randomized into 1 of 3 comparison groups, each to receive a different manual therapy intervention. Immediately following the intervention, subjects will receive post-intervention TMS measures, ankle ROM tests, and lower extremity functional behavior tests, identical to the pre-intervention assessments.

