#### MEP input-output curves

Input-output (IO) curves will be generated by keeping the TMS coil at its optimal hotspot and varying TMS intensity (i.e., input) at 5% intervals from 95% (subthreshold) to 140% (suprathreshold) of MT. At all intensities, 8 single-pulse TMS stimuli will be delivered under each of 2 conditions: (i) at rest and (ii) simultaneous with an active contraction of the muscle (5–10 seconds between stimuli). The order of TMS intensities will be varied randomly.

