#### Ankle range of motion (ROM) measurement

Following the second TMS MT measurement, all subjects will receive 2 different ankle ROM measurements. In the first measurement, subjects will lay prone on a padded table. A single blinded and standardized examiner will measure ankle dorsiflexion ROM with the knee fully extended and then flexed to 90 degrees using a 15.24 cm goniometer in a standard manner.[19] This measurement of ankle ROM demonstrates strong test-retest reliability with knee both flexed (ICC = .97) and extended (ICC = .98).[19] A knee to wall measurement also will be taken.[31] Standing with hand support on the wall, with affected lower extremity anterior and the unaffected lower extremity posterior. Subjects were required to move the knee directly forward to a vertical line on the wall. No attempt will be made to control the height of the medial longitudinal arch during this measurement. For subjects who are unable to touch their knee to the wall (1), the distance from the wall to the anterior aspect of the knee will be measured and recorded in centimeters as a negative value. Subjects who can touch the knee to the wall will move the foot back until the knee could just touch the wall (2). The distance from the wall to the great toe will be recorded in centimeters as a positive value. The knee to wall measurement of ankle ROM also demonstrates strong test-retest reliability (ICC = .97).[31]

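### On the natural reading, post-intervention TMS curves are scaled to a re-measured motor threshold, so a threshold shift can vanish from the midpoint and slope or appear there with the wrong sign

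*Protocol article*

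**What the plan says.** All places are in the protocol article.

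- **Scale.** Motor threshold (MT): "TMS intensities for this study will be expressed as a percentage of MT". MEP input-output curves: the grid is built by "varying TMS intensity (i.e., input) at 5% intervals from 95% (subthreshold) to 140% (suprathreshold) of MT".
- **Justification.** Motor threshold (MT): within a person, "MT is stable across TMS sessions which assures that suprathreshold TMS intensities expressed as a percentage of MT can be reliably compared" between sessions.
- **What is measured when.** Research Design gives the baseline TMS battery as "pre-intervention TMS measures (motor thresholds and input-output curves", and describes the post-intervention tests as "identical to the pre-intervention assessments". Ankle range of motion (ROM) measurement refers to a second MT determination at baseline ("Following the second TMS MT measurement").
- **What carries over.** TMS measurement says that coil location and orientation are carried from baseline to the post-intervention assessment. It says nothing of carrying over the stimulator output.
- **Outcome.** Motor threshold (MT): "Alterations in corticomotor system excitability will be assessed as changes in MEP and cortical silent period duration (CSP) input-output curve characteristics". CSP input-output curves and Data Analysis name three such characteristics: the maximum, the maximal slope and the midpoint intensity.

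**The concern.** MT is itself a measure of corticospinal excitability: it is the weakest pulse that evokes a small response about half the time. The trial's hypothesis is that the intervention changes corticospinal excitability. Stability of MT between untreated sessions therefore cannot guarantee comparability across the intervention, because it presumes that one part of the effect under test does not occur.

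If the post-intervention grid is tied to a post-intervention MT, the ruler moves with the quantity being measured. When MT falls, the post pulses are weaker in absolute terms and the fitted curve is re-expressed on the new scale.

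Three results are at stake:

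- Aim 2 would be read partly from S50 and slope, which can be nulled or reversed.
- The Aim 3 correlations would use the same distorted values.
- Data Analysis attributes any TMS change to central mechanisms when the H/M ratio is constant, so a scaling artefact could receive that label.

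Silent period duration is exposed too. The article says it depends largely on stimulus intensity, and a given percentage of MT would mean different absolute intensities before and after.

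**Working it through.** The plan gives no figure on this point. Its power statement concerns lateral star balance performance and does not enter.

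**Inputs from the article:** Boltzmann curve; grid 95-140% of MT; MT criterion of 50 μV at rest (100 μV active).

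**Assumed, because the article gives no values:** maximum M = 1 mV, S50 = 60 and width k = 5, the last two in % of stimulator output.

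**Formulas**

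- MEP(s) = M / (1 + exp((S50 − s)/k))
- MT = S50 − k·ln(M/0.05 − 1)
- Maximal slope = M/(4k), so on the %MT scale it is proportional to MT/k

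**Baseline.** MT = 60 − 5·ln(19) = 60 − 14.7 = 45.3. S50 = 60/45.3 = 132.5% of MT. Width = 5/45.3 = 11.0% of MT.

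**Case A, proportional gain in excitability of 10%.** S50 = 54, k = 4.5, MT = 40.8. On the re-measured scale S50 is still 132.5% and the width still 11.0%, so the change is exactly zero.

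**Case B, parallel left shift of 5 points.** S50 = 55, k = 5, MT = 40.3. On the re-measured scale S50 = 55/40.3 = 136.6% and the width is 5/40.3 = 12.4%. Maximal slope changes by the factor 40.3/45.3 = 0.89, a fall of 11%. Both look like reduced excitability. A pulse at a nominal 120% of MT drops from 54.3 to 48.3 points of output.

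| | Re-measured MT | Baseline MT as fixed scale |
|---|---|---|
| A: S50 (from 132.5) | 132.5 | 54/45.3 = 119.3 |
| A: slope | no change | 5/4.5, up 11% |
| B: S50 (from 132.5) | 136.6 | 55/45.3 = 121.5 |
| B: slope | down 11% | no change |

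**General direction.** For a parallel shift x, (S50 − x)/(MT − x) > S50/MT, because (S50 − x)·MT − S50·(MT − x) = x·(S50 − MT), which is positive when S50 > MT and 0 < x < MT. The slope ratio is (MT − x)/MT, always below 1. A loss of excitability (x negative) reverses both.

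**Range.** Take MT 40-60, S50 110-130% of MT and x = 2 or 5:

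- Smallest S50 error: MT 60, S50 66, x = 2 gives 64/58 = 110.3%, up 0.3.
- Largest S50 error: MT 40, S50 52, x = 5 gives 47/35 = 134.3%, up 4.3.
- Slope falls by x/MT, from 2/60 = 3.3% to 5/40 = 12.5%.
- On the fixed baseline scale the same shifts move S50 by −3.3 to −12.5 points, the correct sign, with slope unchanged.

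**What survives.** With MT 50, S50 at 120% of MT and a pure 30% rise in the maximum, MT moves only to 49.1. The fitted maximum shows the full +30%, and slope rises. S50 still drifts the wrong way, from 120 to 122.3.

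**The case against.** **The reference MT for the post-intervention grid is not stated.** The grid is defined only as a percentage of MT. TMS measurement places hot spot and threshold finding together in the pre-intervention session, and the hot spot is then carried forward, so the claim that the post tests are the same cannot be literal for every step. If baseline MT were kept, the problem would disappear. This stands as a limit: re-measurement is the natural reading, but it is an inference. It does not rescue the stability argument, which would be unnecessary if baseline MT were kept.

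**MT change may be analysed anyway.** The repeated-measures sentence under Functional behavior and ROM measurements opens with a scope that takes in every TMS variable. A reader might infer that an MT change would go unexamined; the article does not support that. However, the same sentence ends by naming only balance and ROM outcomes, the t-test and reliability sentences name only MEP/CSP data, and the definition of altered excitability rests on curve characteristics. Testing MT separately would not correct S50 or slope.

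**Maximal amplitude is intact.** A reader might infer that Aim 2 as a whole would return a null or reversed answer. That does not follow: a gain change still shows in the maximum. The reservation is that the grid must reach the plateau. In the illustration the top pulse reaches about 66% of maximum at baseline, 1/(1 + exp(−7.5/11.0)), and about 57% after the 5-point shift, 1/(1 + exp(−3.4/12.4)).

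**The sizes are assumed.** This stands. Nothing in the article says how far MT will move, or whether such errors would be visible with 9 per group.

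**Conclusion.** The concern holds, conditionally. If post-intervention intensities are set from a re-measured MT, then S50 and slope, two of the three curve characteristics, can show no change or the wrong sign for the part of an effect that moves threshold. Silent periods at a given percentage of MT are then also compared at unequal absolute intensities. The direction depends only on S50 lying above MT. The size depends on assumed curves: an S50 error of 0.3 to 4.3 points of %MT and a slope error of 3.3% to 12.5% for parallel shifts of 2-5 points, and complete removal for proportional shifts.

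It would go too far to say that the trial will miss or reverse its effect. The article neither states the reference MT nor gives grounds to expect a particular shift, and maximal amplitude and possibly MT itself remain available. The star balance outcome, on which the sample size rests, is untouched. The stability statement remains usable for untreated repeat measurements, but not as grounds for comparing before with after treatment.

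**What to change.** 1. State that the post-intervention pulses use the same absolute stimulator outputs as at baseline, that is, 95-140% of the pre-intervention MT, and say which of the two baseline MT determinations is the reference.
2. Fit the pre and post MEP and CSP curves on that one fixed scale (absolute output or percentage of baseline MT).
3. Name change in resting and active MT as an excitability outcome alongside the curve characteristics.
4. Limit the stability statement to repeat measurements without intervention, which the two baseline measurements can check.

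The cost is wording in the procedure and analysis sections; no extra pulses are needed. The drawback is that, if MT shifts, the post grid no longer spans exactly 95-140% of the current MT. In Case B it would run from 43.0/40.3 = 107% to 63.4/40.3 = 157% of the new MT, so the subthreshold points would be lost.

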#### MEP input-output curves

Input-output (IO) curves will be generated by keeping the TMS coil at its optimal hotspot and varying TMS intensity (i.e., input) at 5% intervals from 95% (subthreshold) to 140% (suprathreshold) of MT. At all intensities, 8 single-pulse TMS stimuli will be delivered under each of 2 conditions: (i) at rest and (ii) simultaneous with an active contraction of the muscle (5–10 seconds between stimuli). The order of TMS intensities will be varied randomly.

#### CSP input-output curves

Silent period durations depend largely on the intensity of the TMS stimulus delivered over the 'hot spot' of a pre-activated target muscle. The active muscle contraction condition will be standardized by (i) using audio-visual feedback provided to the subject for consistent levels of muscle contraction (10% MVC) and (ii) triggering TMS discharge when EMG activation is maintained at 10% MVC. As such, CSP durations will be obtained during IO curve studies. At each trial, the duration of the silent period will be calculated as the time between (i) when rectified EMG activity drops below average pre-TMS EMG activity (10% MVC) and (ii) when rectified EMG activity rises above that average pre-TMS EMG activity.

The relationship between the size of the MEP and the duration of the silent period versus stimulus intensity can be illustrated as a sigmoidal shape. As such, measured characteristics of the IO curve will be extracted using the Boltzmann sigmoidal function to fit the data points by the Levenberg-Marquard nonlinear least-mean-squares algorithm.[29] The Boltzmann equation relating the amplitude (MEP) and duration (CSP) of the response with the stimulus intensity has three parameters: the maximum value (i) MEP_max_, the plateau of the relation, (ii) the stimulus intensity (S_50_) required to obtain a response 50% of the maximum, (iii) and the maximum slope parameter.

#### H-reflex

In order to determine whether potential changes in TMS-assessed corticospinal excitability pre- and post-intervention are spinally and/or centrally mediated the Hoffmann (H) reflex will be performed. The H reflex is considered the electrical analogue of the tendon stretch reflex. Since it bypasses the effects of gamma motoneurons and muscle spindle discharge, it can be used as a method for assessing spinal reflex excitability in intact human subjects before and after intervention.[30] The H-reflex will be elicited using a Cadwell Sierra Wave EMG Nerve Conduction Device (Cadwell Laboratories, Kennewick, WA, USA) by selective electrical stimulation of the Ia fibers of the posterior tibial nerve at the popliteal fossa. In response to afferent nerve stimulation, H-waves can then be recorded as MEPs using surface EMG electrodes over the soleus muscle. Such stimulation can be accomplished by using slow (less than 1 pulse/second), long-duration (0.5–1 ms) stimuli with gradually increasing stimulation intensity. As stimulator intensity increases, the peak-to-peak H-wave amplitude gets larger and a direct short-latency motor response (M-wave) also begins to develop. The M-wave indicates that orthodromic motor fibres are now being directly stimulated at higher intensities. Finally, at supramaximal intensity stimulation, the H-wave disappears because antidromic motor stimulation completely blocks descending H-reflex conduction, and only the direct M-wave can be observed.

#### Electrode placement

Subjects are positioned prone with the leg to mid thigh exposed. The active electrode is placed 1/3 of the distance up from the intermalleolar line to the popliteal fossa (or at the base of the bulk of the calf muscle). The reference electrode is located midline of the Achilles tendon. The skin will be marked in order to decrease the variability of pre-post testing electrode placement. The ground is placed between the stimulator and electrodes (i.e., knee cap, femoral condyle) and the amplifier is positioned at the hip away from electrodes.

#### Stimulation procedure

Stimulation will be at the popliteal fossa with the top prong (cathode) placed in the middle of the fossa and superior to the bottom prong. The "Positive" end of the stimulator (anode) is positioned inferiorly toward the ankle. The arrow on the stimulator points in the direction of the current flow. In this case, we want the current flowing proximally toward spine. With the pulse width for stimulation set at 1 ms, stimulation is started at a low intensity. Intensity is increased in 1 milliampere (mA) increments. The stimulator delivers pulses at regular intervals (pulse width = 1000 ms) to the Ia afferents. Intensity is gradually increased until an H wave appears. At this point, intensity is increased at 1–2 mA per discharge until the H wave reaches maximum, starts to decrease and the M-wave appears. Intensity is now increased in larger increments (5–10 mA) until the H wave completely disappears and the M-wave reaches a maximum.

#### Ankle range of motion (ROM) measurement

Following the second TMS MT measurement, all subjects will receive 2 different ankle ROM measurements. In the first measurement, subjects will lay prone on a padded table. A single blinded and standardized examiner will measure ankle dorsiflexion ROM with the knee fully extended and then flexed to 90 degrees using a 15.24 cm goniometer in a standard manner.[19] This measurement of ankle ROM demonstrates strong test-retest reliability with knee both flexed (ICC = .97) and extended (ICC = .98).[19] A knee to wall measurement also will be taken.[31] Standing with hand support on the wall, with affected lower extremity anterior and the unaffected lower extremity posterior. Subjects were required to move the knee directly forward to a vertical line on the wall. No attempt will be made to control the height of the medial longitudinal arch during this measurement. For subjects who are unable to touch their knee to the wall (1), the distance from the wall to the anterior aspect of the knee will be measured and recorded in centimeters as a negative value. Subjects who can touch the knee to the wall will move the foot back until the knee could just touch the wall (2). The distance from the wall to the great toe will be recorded in centimeters as a positive value. The knee to wall measurement of ankle ROM also demonstrates strong test-retest reliability (ICC = .97).[31]

